### Frequency and plans for auditing trial conduct {23}

The trial is under the oversight of the Ethics Committee of North-Western Switzerland (EKNZ; project ID 2025-00557). Formal auditing procedures are not planned but can spontaneously be announced and performed by the ethics committee. Any modifications to the study protocol (amendments) or occurrence of severe adverse events are reported to the ethics committee by the research team.

### Plans for communicating important protocol amendments to relevant parties (e.g., trial participants and ethical committees) {25}

Substantial changes to the study setup and study organization, the protocol, and relevant study documents are submitted to the ethics committee for approval before implementation. Under emergency circumstances, deviations from the protocol to protect the rights, safety, and well-being of participants may proceed without prior approval of the ethics committee. Such deviations shall be documented and reported to the ethics committee as soon as possible. Non-urgent changes are only implemented following formal approval.

### Dissemination plans {31a}

Following the processing and analyses of collected data, manuscripts containing the findings of the study are planned to be published within 12 months. For the purpose of publication in the public register, the sponsor also ensures that a lay summary of the trial results is entered in BASEC within 1 year of completion or discontinuation of the trial. The entry is made at least in the national languages of Switzerland in which the study participants were recruited.

## Discussion

Despite strong evidence supporting PA as an effective treatment for MDD [35–37], only a minority of individuals with MDD engage in sufficient levels of PA [51]. PA coaching has emerged as a promising intervention strategy and has demonstrated good acceptance among patients in previous work [61]. However, long-term behavior change remains a major challenge [162]. Recent advances in PA behavior change underscore the importance of addressing not only cognitive determinants but also affective processes [64, 65, 72]. Building on the new behavior change advances and the experience of previous research with in-patients [162], the present study introduces a novel PA coaching program tailored to outpatients with MDD. By explicitly fostering positive affective responses to exercise while also addressing cognitive-reflective factors, the intervention seeks to achieve sustainable increases in PA and, thereby, improve mental and physical health as well as overall quality of life. Behavior change is further supported through smart-ring wearable technology, which promotes self-monitoring and real-time feedback. To our knowledge, this is the first PA coaching intervention for individuals with MDD specifically that targets positive affective responses to exercise while simultaneously incorporating smart-ring technology to enhance PA engagement and adherence.

To contextualize the PACOUTPAT approach, findings from a recent personalized PA intervention for outpatients with MDD are considered, as the trial shares several key features with the current intervention and provides relevant insights. Keller-Varady et al. (2023) evaluated a 6-week personalized PA program supported by motivational interviewing (MI) in outpatients with MDD [169]. Like the current trial, their intervention was delivered in person, focused on establishing sustainable PA routines, and used coaching techniques to facilitate behavior change. The intervention group showed a successful increase in moderate-to-vigorous PA, which was maintained at the 3-month follow-up. However, the relatively small sample size raises concerns about the statistical power and generalizability of the findings. Participant feedback emphasized the importance of free access to personalized coaching, structured guidance in PA planning, and the availability of PA options close to patients’ homes. These insights align with core elements of the PACOUTPAT intervention and are likely to enhance its real-world feasibility.

This trial has several important strengths. Its pragmatic, real-world design is embedded within standard day clinic care, enhancing the potential for future implementation. The intervention is built on a solid theoretical foundation guided by the ART. It also builds upon earlier PA coaching research, integrating key learnings and advancing the field by addressing affective processes as critical drivers of sustained PA engagement. Lastly, smart-ring technology provides objective feedback that may strengthen adherence.

Taken together, the findings from this trial may offer valuable insights into PA promotion in individuals with MDD. Embedding affective-reflective PA coaching within routine psychiatric care could serve as a feasible and scalable strategy to counter physical inactivity. In doing so, the intervention holds promise to enhance both mental and physical health outcomes and support long-term lifestyle change in individuals with MDD.

### Trial status

The trial was prospectively registered in the DRKS registry for controlled trials on May 8, 2025 (DRKS00036209), protocol version 2. Recruitment began in June 2025 and is expected to be completed by December 2026. Data collection commenced in June 2025 and is scheduled to conclude in September 2027. For a brief overview of the study timeline and milestones, see additional file 2. This study follows protocol version 2, dated April 25, 2025 (EKNZ; project ID 2025-00557).

## Data Availability

Access to the final, de-identified trial dataset is restricted to the sponsor-investigator (MG) and the affiliated doctoral student (CS) at the Department of Sport, Exercise and Health, University of Basel. No external researchers or third parties have access to the dataset. This restriction is based on the terms outlined in the informed consent form, which specifies that data collected during the PACOUTPAT study may only be used for the purposes stated in the approved study protocol. Consequently, there are no provisions for data sharing beyond the core research team, and no contractual agreements permit broader access. Requests for access to anonymized data for secondary analyses are not granted, in adherence to the ethical commitments made to participants.

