### Assignment of interventions: blinding

#### Who will be blinded {17a}

Because of the behavioral nature of the intervention, participants and researchers cannot be blinded.

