## Statistical methods

### Statistical methods for primary and secondary outcomes {20a}

Descriptive statistics are presented as means (M), standard deviations (SD), medians (Mdn), interquartile ranges (IQR), frequencies, and percentages (%). The primary outcome, device-based PA (Fibion^®^), and the secondary outcomes, depressive symptom severity (HAMD17, BDI-II) and health-related quality of life (SF-12), will be analyzed using linear mixed models (LMMs) with measurements at T1 and T2 as outcomes. Baseline values of the respective outcomes (T0) will be included as predictors, along with a baseline × time interaction to account for potential changes in baseline influence over time. Fixed effects will include group (CG, IG1, IG2), time (T1, T2), and the group × time interaction, with a random intercept for each participant. For the secondary outcomes, device-based PA at the corresponding time point will additionally be included as a predictor to examine whether changes in these outcomes are associated with PA. Estimated marginal means from the LMMs will be used to compare groups at each time point, with Dunnett’s adjustment applied for comparisons of each intervention group versus control.

Although randomization is expected to minimize baseline imbalance, any clinically relevant imbalances observed will be accounted for in adjusted analyses of the primary outcome.

Continuous predictors (e.g., age, BMI, baseline PA) will be examined for potential nonlinear effects and may be modeled using flexible approaches such as natural splines. Model assumptions, including normality of residuals and homoscedasticity, will be checked, and appropriate transformations or alternative methods will be applied if assumptions are seriously violated.

Baseline CRF will be tested as a moderator by including CRF and its interactions with group and time (CRF × group × time) in the LMMs. Models will first be run without CRF to estimate the overall intervention effect.

Implementation outcomes (reach, dose, fidelity, adaptation) and participant satisfaction will be summarized descriptively. Between-group differences (IG1 vs. IG2) will be explored using independent-sample *t*-tests. All statistical analyses are performed using SPSS and Jamovi [163], with the significance level set at *p*
$$\le$$ 0.05. The completed trial will be reported in accordance with the CONSORT 2025 statement [164].

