### Methods in analysis to handle protocol non-adherence and any statistical methods to handle missing data {20c}

All study variables will be screened for missing data, outliers, and multicollinearity. Missing data patterns will be examined descriptively and visually, with Little’s MCAR test as a supplementary tool. The most plausible missing data mechanism (MCAR, MAR, or MNAR) will be inferred from these observations, study design, and theoretical considerations, and sensitivity analyses will be conducted to assess robustness [165]. If data are plausibly MCAR or MAR, appropriate imputation methods (e.g., multiple imputation) will be applied [166].

The primary analysis will follow the intention-to-treat (ITT) principle, including all participants as randomized and using the chosen imputation methods for missing data [166]. This approach estimates the effectiveness of the interventions under real-world conditions [167, 168]. A secondary per-protocol (PP) analysis, including only participants who adhered to the study protocol, will be conducted to estimate the intervention effect under ideal adherence [167].

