## Oversight and monitoring

### Composition of the coordinating center and trial steering committee {5d}

PACOUTPAT is conducted as a single-center trial at the Sonnenhalde AG Psychiatric Clinic. The study is implemented by the Department of Sport, Exercise and Health (DSBG) of the University of Basel at the Sonnenhalde AG site.

The sponsor-investigator (MG) from the University of Basel is responsible for the overall coordination and quality assurance of the trial, including implementation in accordance with the protocol, data management and analysis, staff instruction, and dissemination of findings. Day-to-day trial operations are led by an affiliated doctoral student (CS) who oversees participant recruitment, data assessments, and intervention delivery. The doctoral student is supported by a research assistant who assists with recruitment, data collection, and communication with patients. PA coaches, all with a background in sport and exercise science, are trained by the doctoral student and deliver the intervention according to standardized procedures. The co-principal investigator ([name], chief physician of Sonnenhalde AG) is responsible for the implementation of clinical treatment and the supervision of patients. Furthermore, he ensures favorable recruitment conditions by integrating the intervention into treatment as usual and establishing effective communication between clinic staff and DSBG personnel. Clinic staff support recruitment by informing eligible patients about the study and encouraging contact with the research team.

The study team maintains structured communication through the following:Weekly to monthly meetings between the sponsor-investigator and the doctoral studentWeekly to biweekly meetings between the doctoral student and the research assistantWeekly to monthly meetings between the doctoral student or research assistant and the PA coachesWeekly meetings between the doctoral student or research assistant and the clinic staff

Additionally, an annual team meeting is held with the broader research team, including the sponsor-investigator, co-principal investigator, doctoral student, research assistant, PA coaches, and co-authors, to review study progress and coordinate next steps.

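### Blinding is ruled out for all researchers for a reason that does not cover data processing and analysis, so open analysis choices can be made by people close to the intervention with arm in view

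*Protocol article*

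**What the plan says.** All references are to the protocol article.

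- **Blinding.** Section {17a} states that "participants and researchers cannot be blinded" and gives the behavioural nature of the intervention as the only reason. No masked analyst or arm-free data review is described.
- **Access.** Data Availability states: "Access to the final, de-identified trial dataset is restricted to the sponsor-investigator" and the affiliated doctoral student. It adds: "No external researchers or third parties have access to the dataset".
- **Roles.** Section {5d} gives the sponsor-investigator overall coordination and quality assurance, "including implementation in accordance with the protocol, data management and analysis, staff instruction, and dissemination of findings". The doctoral student leads daily operations and is the person "who oversees participant recruitment, data assessments, and intervention delivery". The doctoral student also trains the coaches.
- **Choices left to the data, {20a}.** Clinically relevant imbalances, once observed, are to be adjusted for in the primary outcome. Continuous predictors may be given splines. For model checks, "appropriate transformations or alternative methods will be applied if assumptions are seriously violated".
- **Choices left to the data, {20c}.** "All study variables will be screened for missing data, outliers, and multicollinearity", with no stated consequence for an outlier. The missing-data mechanism is inferred partly from the observed patterns, and the primary intention-to-treat analysis uses whichever imputation method is then chosen.
- **Timing.** Section {21b} plans no interim analysis but lets each analysis run once data for its own time point are complete.

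**The concern.** Section {17a} rules out a safeguard on a ground that does not reach it. Cleaning an accelerometer file, choosing a scale or deciding how to impute does not require knowing who was coached. Yet the plan gives the dataset only to two people who run the trial, one of them directly involved in delivering the intervention, and several choices affecting the primary result are to be made after data are seen. The adjustment rule in {20a} in fact requires a comparison of arms, because an imbalance can be observed in no other way.

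What is at stake is the credibility of a positive finding. If the arm effect can be seen while scale, covariates and exclusions are still open, a critic can say that the reported analysis was selected, and the plan offers nothing to answer with.

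**Working it through.** **1. Does the reason in {17a} cover the task?** Participants and coaches know the allocation by taking part, so the reason holds for them. Sensor processing and analysis decisions use recorded data only, so it does not hold there. De-identification removes identity; it does not by itself remove allocation.

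**2. What is fixed and what is open?**
- Fixed in {20a} and {20c}: linear mixed model on T1 and T2, baseline and baseline × time, group × time, random intercept, Dunnett comparisons with control, intention-to-treat as primary.
- Already set under the primary outcome in {12}: sleep is excluded using recorded bedtimes.
- Open: transformation or alternative method, covariates for observed imbalance, splines, outlier handling, missing-data mechanism and imputation method.

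**3. Timing.** Trial status expects recruitment to end by December 2026. T1 is 10 weeks and T2 36 weeks after baseline, so for the last participants 36 − 10 = 26 weeks lie between T1 and T2. Under {21b}, T1 effects by arm may be known in that interval, although T1 and T2 enter one primary model.

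**4. Size.** The plan gives no figure on this point. Its sample-size figure, used here only to confirm the settings, reproduces: λ = f²·N·m/(1 − ρ) = 0.175² × 87 × 3/0.50 = 15.99, with 4 and 168 degrees of freedom, gives power 0.903 against the stated 90%.

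Inputs from {14} and {20a}: α = 0.05; r = 0.50; two Dunnett comparisons with control; 114/3 = 38 per arm, or after 30% loss 114 × 0.70 = 79.8, about 27 per arm. Assumed: log-normal activity with log-SD 0.5 to 1.0, no true effect, and a baseline-adjusted ANCOVA at one visit. Familywise error is the share of simulated trials in which either |t| = |estimate|/SE exceeds the Dunnett critical value (2.24–2.25).

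Open options: 3 scales (raw, square root, log) × 4 covariate sets (neither, age, BMI, both) × 2 outlier rules (keep or drop residuals beyond 3 SD) = 24 analyses, with 6,000 trials per setting.

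| Per arm | Log-SD 0.5 | Log-SD 0.8 | Log-SD 1.0 |
|---|---|---|---|
| 27 | 11.2% | 12.8% | 13.6% |
| 38 | 11.5% | 14.0% | 14.6% |

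The entries are the share of trials with at least one significant analysis. A single raw-scale analysis gives 3.8–4.8%.

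A second set-up (about 80 evaluable, log-SD 0.6, four weakly prognostic covariates, 4,000 trials) gave 4.8% for one fixed analysis, 6.7% with scale free, 10.6% with scale and one covariate free, and 15.2% with an outlier cut-off also free.

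**5. Which kind of masking helps?** In separate null simulations of this kind:
- arms labelled, most favourable analysis taken: about 10–13.5%;
- arms coded A/B/C, analysis with the largest difference between any two codes taken, then unmasked: about 10–13%;
- scale chosen on data without arm, covariates and outlier handling fixed: about 5%.

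The reason is simple. Letters still show how far apart the groups are, so one can still select the analysis with the largest separation. A pooled file carries no information on the difference between arms.

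**The case against.** **Rules on outliers, transformation and imputation usually sit in an analysis plan, which is not shown.** This is the strongest objection, and it stands as far as missing detail goes. It does not answer the point. Who is blinded is a protocol matter, and {17a} settles it too broadly. The article also says outright that these choices will follow from observed data.

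**Most of the inflation comes from not fixing the analysis, and coded arms would barely reduce it.** This stands, and it shapes the fix: the arm variable has to be absent, and covariates have to be fixed.

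**The documents do not say that decisions are made on arm-labelled data, or that the sponsor-investigator knows individual allocations.** Also correct. Arm visibility is an inference. It is firm for the imbalance rule and for residuals from a model with a group term, and weaker for the missing-data screening. Being responsible for analysis does not show who runs it.

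**The simulations are generous to the concern.** They use one visit rather than the planned mixed model, assume the skewness, do not vary splines or imputation, and ignore the condition that assumptions be seriously violated. They also switch age and BMI on and off, whereas {20a} names these only as examples of predictors to check for nonlinearity. All of this stands, and the figures are worst cases.

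Three stronger readings are tempting and not supported. Sleep removal is not an open choice, since recorded bedtimes set it. The device-based outcome has not lost its protection: it still guards against assessment bias, which is a different matter from analyst choice. And nothing suggests that anyone intends to choose favourably.

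**Conclusion.** The point holds in limited form, as a cheap improvement rather than a flaw that invalidates the design. Section {17a} excludes masking for work that could be masked, the two people with data access are close to the trial and its coaching, and a defined set of choices is left to observed data, possibly with T1 effects already known. The link to the coaching is the doctoral student's; the sponsor-investigator's is overall leadership.

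On assumed skewed data the worst case is a rise in familywise type I error from about 5% to about 10–15%. A reader might take that as this trial's error rate. It is not: it is reached only if the most favourable analysis is always taken, and it depends on the assumed skewness and option set. The more useful result is the contrast between coding the arms (about 10–13%) and removing them with the remaining options fixed (about 5%).

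**What to change.** 1. **Section {17a}:** state that participants and coaches are not blinded, but that decisions on valid days, outliers, scale or method, functional form and missing-data handling are made and dated on a pooled file. In that file the arm variable is removed, not merely coded, and the IDs are replaced. Coach records, ring data and satisfaction data, which reveal arm, are kept apart. The decisions are completed before the first T1 analysis.
2. **Section {20a}:** replace adjustment of the primary outcome for observed imbalances by covariates fixed in advance, namely baseline PA and the stratification factors age and sex. Any further adjustment becomes a sensitivity analysis.
3. **Section {16b} and Data Availability:** let the staff member who prepared the envelopes hold the arm variable until the decisions are dated. Both places need amending, because {16b} limits that person to data monitoring and Data Availability limits the dataset to two people.

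The cost is one dated memo, a small file-preparation step and the wording changes, with no extra staff or visits. Data collection runs to September 2027, so this can be set now, provided that it precedes the first T1 analysis. Masking will be imperfect, because the doctoral student oversees assessments and may recognise some participants from their characteristics.

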## Abbreviations

7DPAR: 7-Day Physical Activity Recall
AFFEXX: Affective Exercise Experiences
ANOVA: Analysis of variance
ART: Affective-Reflective Theory of physical inactivity and exercise
BCT(s): Behavior change technique(s)
BDI-II: Beck Depression Inventory II
BMI: Body mass index
CG: Control group
CRFs: Case report files
DALYs: Disability-adjusted life years
DSBG: Department of Sport, Exercise and Health, University of Basel
EKNZ: Ethikkommission Nordwestschweiz (Ethics Committee of Northwestern Switzerland)
F32: Depressive episode (ICD-10)
F33: Recurrent depressive disorder (ICD-10)
FAS: Felt Arousal Scale
FS: Feeling Scale
HAMD-17: Hamilton Depression Rating Scale
ICD-10: International Classification of Diseases, Tenth Revision
IG: Intervention group
ITT: Intention-to-treat
LMM: Linear mixed models
LPA: Light physical activity
MCAR: Missing completely at random
MCID: Minimal clinically important change
MDD: Major depressive disorder
MI: Motivational interviewing
MoVo: Motivation-volition
MPA: Moderate Physical Activity
MRC: Medical Research Council
MVPA: Moderate-to-vigorous physical activity
NTC: Negative temperature coefficient thermistor
PA: Physical activity
PACINPAT: Physical activity counselling in in-patients with major depressive disorder
PACOUTPAT: Physical activity coaching in outpatients with major depressive disorder
PAR-Q: Physical Activity Readiness Questionnaire
PP: Per protocol
PSDQ: Physical Self-Description Questionnaire
RCT: Randomized controlled trial
SF-12: Short Form-12 Health Survey
SSK-scale: Self-Concordance Scale
ST-IAT: Single-Target Implicit Attention Test
VO2max: Maximal oxygen uptake
VPA: Vigorous physical activity
WATCH: Wearable Activity Tracker Checklist for Healthcare
WHO: World Health Organization
